### Study design

This is a prospective observational, repeated measurement, single-subject design study.

Changes in speech recognition by noise score, health-related quality of life, and overall well-being are assesses.

The study design is monocentric and is conducted at the outpatient service of the ENT Department of the “Saliceto” Hospital in Piacenza, Italy.

All the materials used are appropriate for the italian language.

This study is registered with the Ethics Committee of the Area Vasta Emilia Nord under number 104; date of approval 17/07/2017.

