## Discussion

This study aims to show the potential positive effect of HAs on auditory skills and on quality of life of older adults with hearing loss. In particular, the efficacy of HA in speech perception in noisy environments and the improvement of quality of life in the older adults using HA for the first time is to be evaluated. The broad approach will lead to a greater understanding of how hearing impacts the quality of life in older adults thereby improving healthy aging.

Since the older adults are increasing in number in the Italian population, a greater number of hearing aids will be required to treat this growing presbycusic population. This will strongly affect the finances of the National Health System, which bears the full or partial cost of HA in most cases. This is also a good reason to understand the real benefits of the HA application clearly. The study outcomes are intended to provide transparent and comparable evidence-based information for healthcare policymakers by supporting the provision of health services for the treatment of hearing loss.

The comprehensive protocol considers a range of widely accepted, interrelated metrics associated with aging in addition to functional hearing. The use of this protocol does not propose the investigation of causal effects but rather investigation of the pre-post HA candidates by observing long-term health outcomes.

The primary endpoint of this study is to identify significant improvement in speech recognition in noise. The percentage of subjects with SNR > 1.5 dB at OLSA test is to be evaluate in order to verify the endpoint.

The OLSA test is the tool most frequently used to find the auditory outcome in noisy environment in the majority of the recent literature. Use of this test has overcome the traditional speech audiometry because it uses sentences consisting of a matrix of 5 semantically unpredictable words and is based on an adaptive method. This has overcome the memory capacity of HA users who perform speech audiometry several times at follow up and are able to learn the words in the lists. Furthermore, in contrast to speech audiometry with sentences of common use that have a semantic context, the OLSA test does not have a predictable semantic context.

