During this study two-time point, tonal unaided audiometry was used to check any auditory threshold modification and worsening of the audiometric clinical situation over time. Speech audiometry in unaided conditions in the first assessment and in aided conditions in the second assessment were used because it describes the sample and allows it to be compared to the existing literature.

The second objective of this study is based on the evaluation of possible improvements in the overall health-related quality of life in the sample.

To verify this aim, self-report questionnaires were chosen, which are essentially non-verbal and consequently remove challenges directly associated with utilizing new HA. The percentage of subjects who improve the questionnaire score using HA (second assessment) compared to the first evaluation in unaided conditions is to be evaluated.

Improvement in quality of life can be evaluated by using different questionnaires. The AQoL questionnaire is used in this study because of its robust psychometric characteristics and wide diffusion in the health-related quality of life literature. In a review by Mihalopoulos et al., (thatanalyzesinstruments for depression outcome measurements) report that AQoL-8D “had the highest correlation with the disease-specific measurements and the best goodness-of-fit transformation properties” [28].

The HHIE has been included in the study in order to better understand the effects of hearing impairment on emotional and social adjustment in everyday life. It is one of the most widely applied questionnaires with respect to auditory participation and has been reported with both HA and cochlear implant recipients [41]. A significant reduction of the questionnaire score in Post vs. Pre-evaluation is expected in this study, which suggests quality of life improvement.

The MoCA questionnaire was chosen to screen the cognitive abilities of subjects. The use of this questionnaire will exclude deficits in these abilities. Using this test in Pre and Post evaluation will verify that cognitive abilities do not affect other questionnaires and HA results. The use of the MoCA questionnaire in the Pre and Post evaluation will exclude a reduction of the cognitive abilities over time. A reduction of these abilities can be a sign of the deterioration of the general state of health that may affect the execution of the other questionnaires used. The same score is expected in Pre and Post evaluation of the same subject.

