The APHAB questionnaire is used to assess problems in speech understanding in different listening situations. This self-assessment is one of the most used questionnaires in clinical practice. An improvement in the scores in Post evaluation compared to Pre evaluation will verify a reduction of listening problems secondary to HA usage.

The IOI-HA questionnaire is only used in the Post evaluation. It will help understand the difficulties and benefits of HA use perceived by the patients. In particular, this questionnaire will give us a picture of the HA outcomes in different areas. Furthermore, being a standardized questionnaire, it will facilitate comparison of the sample with the existing literature.

The strength of this study lies in evaluating the auditory and health outcomes over time which contrasts with most of the recent studies that show an overview of the outcomes at a precise moment and various other biased sources.

Furthermore, as reported by Hanratty and Lawlor, people over 70 are thought to have a hearing impairment that would benefit from a HA but a high percentage of these people probably never use their aid [12]. The study presented in this paper can not only underline the benefits but also real HA usage over time. This information is very important for healthcare policy because the Italian National Health System bears all or some of the HA costs for most of these patients.

These outcomes should contribute to providing key actors of the health system with means of enhancing their part in a collective endeavor targeting the best care and quality of life for older adults citizens because general well-being translates into healthy aging.

The single-subject, repeated-measures design allows for subjects to serve as their own controls, and thus increases statistical power. The relatively large population size helps provide a good estimate of effect size and would make the results broadly applicable.

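### The Discussion disclaims causal effects, yet fixes in advance that an APHAB improvement verifies an effect of the hearing aid, which a single-group before-after design cannot show

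*Protocol article*

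**What the plan says.** All references are to the protocol article.

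- **Disclaimer (Discussion).** "The use of this protocol does not propose the investigation of causal effects but rather investigation of the pre-post HA candidates".
- **APHAB conclusion (Discussion).** An improvement from Pre to Post "will verify a reduction of listening problems secondary to HA usage". The APHAB section under Materials calls the plain Pre minus Post difference a measure of benefit.
- **Efficacy wording (Discussion).** Among the things to be evaluated is "the efficacy of HA in speech perception in noisy environments".
- **HHIE (Discussion).** "A significant reduction of the questionnaire score in Post vs. Pre-evaluation is expected in this study, which suggests quality of life improvement". The second objective is to be verified by the percentage of subjects whose questionnaire score improves.
- **Design (Study design).** "This is a prospective observational, repeated measurement, single-subject design study". The Discussion adds: "The single-subject, repeated-measures design allows for subjects to serve as their own controls".
- **Timing and entry (Abstract, Timing schedule, Subjects).** Pre is taken just before first use of the aid and Post after one year. About 100 first-time users are identified consecutively from the local health service's hearing-aid registry. No group without an aid is described.

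**The concern.** To say that a reduction is secondary to hearing-aid use is to say that the aid caused it. To say that an improvement will verify this settles the reading of a positive result before any data are seen. The same Discussion says that causation is not under study, so a reader cannot tell which conclusion the trial is entitled to draw.

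The design supports only the weaker one. APHAB is a self-assessment, and the wearer knows whether an aid is in use. With no unaided follow-up, a fall in reported problems could reflect the aid, the expectation of benefit, a changed internal standard when answering a year later, or an entry score that was unusually high. Using subjects as their own controls removes stable differences between people. It does not remove any of these.

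The Discussion addresses the results to healthcare policymakers and to the question of public funding. If the APHAB sentence is followed as written, an uncontrolled change would reach them as a verified effect of the device.

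**Working it through.** **1. The passages side by side**

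| Place | What it lets the study conclude |
|---|---|
| Discussion, disclaimer | Before-after description; no causal effect |
| Discussion, APHAB paragraph | Fewer listening problems, caused by the aid |
| Materials, APHAB section | Raw Pre minus Post difference, labelled benefit |
| Discussion, efficacy phrase | Efficacy of the aid for speech in noise |
| Discussion, HHIE paragraph | A lower score suggests better quality of life; cause not stated |

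The first two rows cannot both hold. The contradiction is textual and needs no arithmetic.

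**2. How easily a non-aid shift becomes significant (illustration)**

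The article gives no expected change, SD or test-retest correlation for APHAB, so there is no planned figure to reproduce. The only input taken from it is n = 100. Assumed: a true aid effect of zero, a two-sided 5% paired t-test, and a shift of d (in SDs of the individual change) from causes other than the aid. The article assigns questionnaires a nonparametric test, so the results are approximate.

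P(significant improvement) = 1 − F(t₀.₉₇₅,₉₉), where F is the noncentral t distribution with 99 df and noncentrality d√100 = 10d. The share of subjects improving on a continuous score is Φ(d).

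| d | P(significant improvement) | Share improving |
|---|---|---|
| 0 | 0.025 | 50% |
| 0.1 | 0.166 | 54% |
| 0.2 | 0.508 | 58% |
| 0.3 | 0.844 | 62% |

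The null rate is 2.5%, because only significance in the direction of improvement is counted. The last column bears on the percentage of improvers: with no change at all, about half would improve, and the Discussion gives no reference rate.

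**3. Regression to the mean alone (illustration)**

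Suppose the group's mean score at entry lies e SD above the mean of the population it comes from, and the test-retest correlation is r. The expected fall is e(1 − r) SD, the SD of the change is about √(2(1 − r)), and d is their ratio. For e = 0.5 and r = 0.8: fall 0.10, SD √0.4 = 0.632, d = 0.158, P = 0.347.

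| r | e = 0.25 | e = 0.5 | e = 1.0 |
|---|---|---|---|
| 0.6 | 0.197 | 0.600 | 0.993 |
| 0.7 | 0.158 | 0.483 | 0.970 |
| 0.8 | 0.120 | 0.347 | 0.879 |
| 0.9 | 0.080 | 0.197 | 0.600 |

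Here e is an excess over a population mean. If it were instead a temporary excess over the subjects' own usual level, the expected fall would be the whole of e. At e = 0.25 that gives d = 0.25/√0.6 = 0.323 and P of about 0.89 for r = 0.7, and d = 0.25/√0.4 = 0.395 and P of about 0.975 for r = 0.8. Neither e nor r is in the documents.

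**The case against.** The best defence is that the study is openly observational, disclaims causation, and has one over-strong sentence about a questionnaire that the Abstract does not list among its main indicators. Much of this stands, and it limits the point in four ways.

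- **Scope.** A reader might infer that the protocol claims a verified causal benefit for every self-report outcome. It does not. The verifying sentence is about APHAB only. The HHIE wording is softer and does not name the aid as cause. In "the efficacy of HA in speech perception in noisy environments and the improvement of quality of life in the older adults using HA", efficacy governs speech in noise, which is the OLSA performance test, while quality of life is given only as improvement among users.
- **Entry level.** A reader might infer that subjects join at a peak of perceived handicap, so that regression to the mean is certain. The documents do not say so. Entry is through the registry, with a better-ear pure-tone average of at least 45 dB HL and no questionnaire cut-off. A raised entry score is possible, but it is an inference.
- **Direction.** A reader might infer that any bias must favour the aid. Hearing may worsen over the year, which would work the other way; unaided audiometry is repeated to look for this. Candidates with unrealistic expectations are excluded, which reduces expectation bias without removing it.
- **Design.** A reader might infer that the lack of a control group is itself an error. A declared single-group observational study is legitimate.

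None of this reconciles the APHAB sentence with the disclaimer.

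**Conclusion.** The point holds as a conflict between the stated conclusion and both the design and the article's own disclaimer. A Pre-Post APHAB change can show how reported listening problems moved over 12 months in first-time users. It cannot verify that the aid caused the movement.

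Its size cannot be taken from the documents. On the stated assumptions, a non-aid shift of 0.1 to 0.3 SD of the change, with no aid effect, gives a significant improvement in about 17% to 84% of studies of 100 pairs, against 2.5% without a shift. This shows that modest shifts are enough; it is not an estimate of the bias in this trial, whose net direction is uncertain. The conclusion rests on the wording and the single-group design, not on these figures.

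The correction should be made, but it concerns what may be concluded, not how the study is run.

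**What to change.** 1. In the APHAB paragraph of the Discussion, replace the verifying statement with: *will describe change in reported listening problems over 12 months in first-time HA users, not attributable to the aid alone*. Read the term benefit in the APHAB section under Materials in the same sense.
2. Interpret the HHIE-S and AQoL changes, and the percentage of subjects who improve, in the same way.
3. Bring the efficacy phrase in the Discussion into line with the disclaimer in that section.
4. Name unblinded self-report and regression to the mean as alternative explanations.

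This needs no new subjects, visits, data or analyses. The cost is a less favourable headline claim.

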## Data Availability

Data can be obtained by the corresponding author upon request.

## Abbreviations

APHAB: Abbreviated Profile of Hearing Aid Benefit
AQoL: Assessment of Quality of Life
IOI-HA: International Outcome Inventory for Hearing Aids
HA: Hearing Aids
HHIE-S: Hearing Handicap Inventory in the Elderly Screening test
MoCA: Montreal Cognitive Assessment
PTA: Pure Tone Audiometry
SRT: Speech Reception Threshold
